## Abstract

**Background:**

Bipolar disorder is a source of marked disability, morbidity and premature death. There is a paucity of research on personalised psychosocial interventions for bipolar disorder, especially in low-resource settings. A pilot randomised controlled trial (RCT) of a culturally adapted psychoeducation intervention for bipolar disorder (CaPE) in Pakistan reported higher patient satisfaction, enhanced medication adherence, knowledge and attitudes regarding bipolar disorder, and improvement in mood symptom scores and health-related quality of life measures compared with treatment as usual (TAU).

**Aims:**

The current protocol describes a larger multicentre RCT to confirm the clinical and cost-effectiveness of CaPE in Pakistan. Trial registration: NCT05223959.

**Method:**

A multicentre individual, parallel-arm RCT of CaPE in 300 Pakistani adults with bipolar disorder. Participants over the age of 18, with a diagnosis of bipolar I or II disorder who are currently euthymic, will be recruited from seven sites: Karachi, Lahore, Multan, Rawalpindi, Peshawar, Hyderabad and Quetta. Time to recurrence will be the primary outcome assessed using the Longitudinal Interval Follow-up Evaluation (LIFE). Secondary measures will include mood symptoms, quality of life and functioning, adherence to psychotropic medications, and knowledge and attitudes regarding bipolar disorder.

**Results:**

This trial will assess the effectiveness of the CaPE intervention compared with TAU in reducing the time to recurrence for people with bipolar disorder currently in remission in Pakistan and determine the effect on clinical outcomes, quality of life and functioning.

**Conclusions:**

A successful trial might lead to rapid implementation of CaPE in clinical practice, not only in Pakistan, but also in other low-resource settings, including those in high-income countries, to improve clinical outcomes, social and occupational functioning, and quality of life in South Asian and other minority group patients with bipolar disorder.

Bipolar disorder affects 40 million people worldwide, with a significant disease burden attributed to low- and middle-income countries (LMICs).^1^ It is a highly recurrent condition, with poor recovery between episodes of illness.^2^ Onset is usually in early adult life and over a lifetime bipolar disorder is associated with significant psychosocial impairment and economic costs.^3^ Worldwide, approximately 43% of people with bipolar disorder report suicidal ideation, 21% have a plan for suicide and 16% attempt suicide.^4^ Recurrence rates and hospital admissions for people with bipolar disorder remain high despite advances in psychopharmacology and psychosocial interventions. The Global Burden of Disease studies attributed 9.9 million years lived with disability (YLD) to bipolar disorder between 1990–2010, making it the 16th leading cause of YLD worldwide.^3^ In the USA, the total management and treatment cost for persons with bipolar disorder in 2009 was estimated to be US$151 billion and the cost per patient ranges from US$1904 to $33 090 annually.^5^ Although pharmacotherapy is essential for the successful treatment of bipolar disorder, adjunctive psychosocial interventions are effective for acute depressive episodes, maintenance treatment, relapse prevention and restoration of quality of life to the individual and their family.^6,7^

There is minimal access to psychological and medical treatments for mental health problems in Pakistan.^8^ The psychopathology, incidence, prevalence and course of bipolar disorder are poorly described in LMICs, including Pakistan, although cross-sectional surveys indicate that the prevalence of bipolar spectrum disorders may be as high as 14% in Pakistani youth.^9,10^ Three-quarters of the global burden of mental, neurological and substance use disorders, including bipolar disorder, lies within LMICs, yet 90% of this population do not have access to appropriate mental healthcare^3^ or to mental health research, which is the foundation for building evidence-based, person-centred services. People with mental disorders such as bipolar disorder are far more likely than the general population to die as a consequence of their untreated mental or physical health problems.^11^ There is an urgent need to support research that may enhance the practice of health workers in this setting. There is a need to provide evidence for interventions that can empower patients with knowledge about their mental health in order to achieve and maintain recovery. In Pakistan, the economic burden of mental disorders, including bipolar disorder, was conservatively estimated at over $4 billion in 2006.^12^ This imposes a significant strain on the economy and on severely constrained mental healthcare spending, which in Pakistan is 0.004% of total healthcare spending.^13^ Economic growth and stability in Pakistan are a top priority for the country, but high rates of mental health problems such as bipolar disorder pose a sizeable challenge to this emerging economy.^14^ The World Bank's third edition of disease control priorities includes mental health conditions since effective treatment of these is likely to deliver the greatest economic and social benefit in low-resource settings, reducing disability and enhancing productivity.^15^ There is an urgent need to provide culturally appropriate, evidence-based interventions that can be delivered feasibly in low-resource settings.

## Psychoeducation for bipolar disorder

Evidence suggests that psychoeducation is an effective adjunctive treatment option in bipolar disorder.^16^ Psychoeducation broadly includes providing the patient and family with information about the nature of the illness, its treatments and key coping strategies.^17^ Psychoeducation is an integral part of treatment for psychiatric disorders, which can improve treatment adherence and reduce the risk of recurrence and consequent hospital admission.^18^ Structured psychoeducation programmes include the provision of information about the course and characteristics of the illness (e.g. recurrence rates, trigger factors for recurrence, early recognition of recurrence, symptom management, risk of suicide), treatment (e.g. medication and its side-effects, importance of adherence), lifestyle factors (e.g. stress management, avoidance of substance use) and other key issues (e.g. relevance of pregnancy).^17^ Psychoeducation can be delivered to groups or individuals and it is a pragmatic and cost-effective intervention.^19^ Several systematic reviews have concluded that psychoeducation is an effective form of psychotherapy for bipolar disorder.^20^ A recent network meta-analysis of adjunctive psychotherapy in bipolar disorder showed that psychoeducation was superior to standard care alone in preventing illness recurrence.^21^ Of note, only three small psychoeducation trials included in this meta-analysis were conducted in LMICs.^7,22,23^ Findings from small pilot studies in LMICs indicate that individual psychoeducation may be superior to group psychoeducation in these settings.^7^

We led the first randomised controlled trial (RCT) of a culturally adapted psychoeducation intervention (CaPE) for bipolar disorder in Pakistan.^24^ The results of this pilot RCT showed that CaPE was acceptable and feasible for Pakistani patients with bipolar disorder. Retention in the study was good (79%) and 89% of participants in the CaPE group attended all 12 sessions. Patient satisfaction was higher in the CaPE group relative to TAU (the control condition) (effect size e.s. = 1.41). Further, there were large effect sizes shown for CaPE versus TAU on medication adherence (e.s. = 0.81), knowledge and attitudes regarding bipolar disorder (e.s. = 0.68), mania (e.s. = 1.18), depression (e.s. = 1.17) and quality of life measures (e.s. = 0.88). An adequately powered and longer-duration multicentre RCT is now required to assess the clinical and cost-effectiveness of the CaPE intervention. Building on the successful completion of the pilot RCT, we propose a confirmatory RCT to determine the clinical and cost-effectiveness of CaPE for adults with bipolar disorder, delivered by trained therapists across seven centres in Pakistan. This project has the potential to benefit people with bipolar disorder in the short term by improving mental health. Given the devastating long-term effects of bipolar disorder, and the pivotal stage of life at which it usually manifests, the potential longer-term benefits of the project are enormous. Clinical and cost-effectiveness data will inform the evidence base for scalable interventions for bipolar disorder in low-resource settings not only in Pakistan but also in other countries.

## Study objectives

To determine the effectiveness of the CaPE intervention compared with TAU in reducing the time to recurrence for people in Pakistan with bipolar I or II disorder currently in remission.To determine the effect of the CaPE intervention compared with TAU on clinical outcomes, quality of life and functioning.To estimate the cost-effectiveness of CaPE in a low-resource setting (i.e. Pakistan) (if the RCT confirms the effectiveness of CaPE in bipolar disorder).To explore participants’ and therapists’ perspectives on the perceived usefulness of the proposed intervention and to identify the barriers and facilitators of incorporating the intervention into routine clinical practice through process evaluation.

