#### Cost–utility analysis

A cost–utility analysis from healthcare system and societal perspectives will be conducted to establish the cost-effectiveness of CaPE compared with TAU. The treatment groups will be compared with each other at baseline and then at subsequent follow-ups at 3, 6 and 12 months. EuroQol-5D data will be collected at these time points to measure patient quality of life; quality adjusted life-year (QALY) gains between groups will then be estimated and compared at baseline and at the end of the 12-month period. The costs of delivering CaPE and TAU will be collected and will include costs of staff time, including that of therapists and their training to deliver the intervention, resources and equipment used, and any remuneration given to patients for their time. Data on the direct and indirect costs to patients will be collected using a bespoke questionnaire and will include any additional equipment/aids paid out-of-pocket by patients for the sessions as well as time taken off work by the patient and the carer (if any) to attend sessions. Additional data regarding health service use and direct costs to the healthcare system will also be obtained using the Client Service Receipt Inventory, completed by both treatment groups at 3, 6 and 12 months. We will use standard published sources for unit costs where available and supplement this with local sources to convert resource use into monetary values. Costs will be adjusted for inflation to 2025 Pakistani rupees using appropriate inflators. To estimate the cost-effectiveness of CaPE, an incremental cost-effectiveness ratio will be calculated, defined as the difference in costs divided by the difference in QALYs between the treatment groups. Standard procedures will be followed for imputation of missing values as well as for analysis of uncertainty and non-normal distributions. Further statistical analysis of costs will be performed to test for statistical significance of results, and bootstrapping will be performed to estimate variability in key parameters. The robustness of each treatment will be shown through 95% confidence intervals around the cost-effectiveness ratio, with sensitivity analyses.

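### The cost-effectiveness objective is conditional on a positive trial in one place and unconditional elsewhere, and the planned confidence interval around the cost-effectiveness ratio can be unbounded or ambiguous in sign

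*Protocol article*

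**What the plan says.** The protocol article speaks to the economic evaluation in four places.

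- Study objectives, third objective: cost-effectiveness will be estimated "if the RCT confirms the effectiveness of CaPE in bipolar disorder".
- Abstract, Aims: the article describes "a larger multicentre RCT to confirm the clinical and cost-effectiveness of CaPE in Pakistan". No condition is attached. The closing paragraph of the introduction (under Psychoeducation for bipolar disorder) states the same aim, again without a condition.
- Cost–utility analysis: "A cost–utility analysis from healthcare system and societal perspectives will be conducted to establish the cost-effectiveness of CaPE compared with TAU". Again there is no condition.
- Appendix 3: EQ-5D and the service-use inventory are scheduled for follow-up at 3, 6 and 12 months. The Cost–utility analysis section says both groups complete the inventory.

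The Cost–utility analysis section defines the incremental cost-effectiveness ratio as "defined as the difference in costs divided by the difference in QALYs between the treatment groups" and presents its uncertainty through "95% confidence intervals around the cost-effectiveness ratio, with sensitivity analyses". It also plans bootstrapping. On QALYs it says that "quality adjusted life-year (QALY) gains between groups will then be estimated and compared at baseline and at the end of the 12-month period".

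**The concern.** There are two separate problems and one wording slip.

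First, the conditional and unconditional statements cannot both govern. Under the conditional one, costs and QALYs are reported only when the primary test succeeds. A null result on time to recurrence does not settle the economic question, because costs and utilities are different outcomes, so useful data would go unused. When the result is reported, it comes only from trials that landed on the favourable side of the primary test. Any correlation between the primary estimate and the QALY difference then pushes the reported QALY difference upward.

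Second, a ratio is a poor scale for an interval when its denominator may be close to zero. The ratio then grows without limit, and its sign stops being informative. A negative ratio can mean that CaPE is cheaper and better or that it is dearer and worse.

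Third, no QALYs have accrued at baseline, so no gain can be compared there.

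The article expects its clinical and cost-effectiveness data to inform scalable interventions in low-resource settings, so the form of the economic result matters beyond this trial.

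**Working it through.** **Step 1: the plan's own power figure.** The chance of primary success is what would trigger a conditional economic analysis. Inputs from Sample size and Statistical analysis: 120 per arm, mean time to recurrence 21.4 and 34.2 weeks, 12 months of follow-up (52 weeks), two-sided alpha 0.05, stated power 0.91 at a hazard ratio of 1.60. Hazard ratios above 1 favour CaPE, as in the article.

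With exponential times, the event probabilities are 1 − exp(−52/21.4) = 0.912 and 1 − exp(−52/34.2) = 0.781. Expected events are 120 × (0.912 + 0.781) ≈ 203. Power = Φ(√203 × ln 1.60 / 2 − 1.96) = Φ(1.39) ≈ 0.918. The stated 0.91 is reproduced.

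**Step 2: selection, if the condition governs.** I take confirmed effectiveness to mean a significant primary result in favour of CaPE; the article does not define it. About 202 events were used, so SE(log HR) = 2/√202 = 0.141. Let c = 1.96 − ln(HR)/0.141. The economic result is reported with probability 1 − Φ(c), and the mean shift in the QALY difference is ρ × φ(c)/(1 − Φ(c)) of its own standard errors. The correlation ρ between the two estimates is not in the document; 0.3 to 0.6 is assumed.

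| True HR | Probability economic result is reported | Upward shift in QALY difference (SE) |
|---|---|---|
| 1.60 | 0.92 | 0.05–0.10 |
| 1.49 | 0.81 | 0.10–0.20 |
| 1.30 | 0.46 | 0.26–0.52 |

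Check at 1.30: ln 1.30 / 0.141 ≈ 1.865, c ≈ 0.095, φ(c)/(1 − Φ(c)) ≈ 0.397/0.462 ≈ 0.86. Multiplying by 0.3 and 0.6 gives 0.26 and 0.52.

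**Step 3: standard error of the QALY difference.** SE = SD × √(2/120). The document gives no QALY SD. For assumed SDs of 0.15, 0.20 and 0.25 the SE is 0.019, 0.026 and 0.032. The shifts in step 2 then amount to about 0.001–0.003 QALY at HR 1.60 (0.05 × 0.019 to 0.10 × 0.032) and 0.005–0.017 at HR 1.30 (0.26 × 0.019 to 0.52 × 0.032).

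**Step 4: how often the denominator is a problem.** For an assumed gain d, the probability that the estimated difference is negative is Φ(−d/SE). This is also roughly the share of negative bootstrap replicates when the observed gain equals d. The probability that the 95% interval for the QALY difference includes zero is Φ(1.96 − d/SE) − Φ(−1.96 − d/SE). When it includes zero, the 95% set for the ratio is not an ordinary bounded interval.

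| Assumed gain | Negative difference, SD 0.15 to 0.25 | Interval includes zero, SD 0.15 to 0.25 |
|---|---|---|
| 0.03 | 6% to 18% | 0.66 to 0.85 |
| 0.05 | 0.5% to 6% | 0.27 to 0.66 |
| 0.08 | under 1% | 0.02 to 0.30 |

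Example: d = 0.03, SD 0.25 gives Φ(−0.03/0.0323) = Φ(−0.93) ≈ 0.18.

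**Step 5: does primary success remove the ratio problem?** In a simulation at HR 1.60 with SD 0.20, the probability that the QALY interval includes zero, given primary success, is about 0.77 for a gain of 0.03 (0.79 without conditioning) and 0.47–0.49 for 0.05 (0.51 without). A significant effect on time to recurrence does not move the QALY difference clearly away from zero.

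**The case against.** The strongest reply on the first part is that the Method text is the operative one and is unconditional. The abstract and introduction agree with it, the data are collected in both arms, Randomisation and masking commits to publishing whatever the outcome, and quality of life is an objective in its own right without any condition. This stands. A reader might infer that the economic result is selected on success as a settled fact. The documents show only that two statements conflict, and selection follows only if the one in Study objectives governs.

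A reader might also carry over the familiar inflation of significant estimates. At a true hazard ratio of 1.30 the mean significant estimate is about 1.47, a 46% overstatement on the log scale (ln 1.47 / ln 1.30 ≈ 1.46). The hazard ratio does not enter the cost-effectiveness ratio, and that inflation would be the same with or without the economic condition. The relevant quantity is the shift in the QALY difference, which is small at the design effect.

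On the interval, it is fair to say that bootstrapping and sensitivity analyses are already planned, and that thresholds and acceptability curves are commonly left to a fuller plan. Their absence is therefore not the fault. What remains is that the article names the interval around the ratio as the way to present uncertainty. If the true gain is large the interval may be perfectly usable, so the claim is that it can fail, not that it will.

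Finally, the loose sentence on QALYs does not show that the wrong calculation is intended. EQ-5D is collected at all the time points that an area-under-the-curve calculation needs. How QALYs are computed and adjusted for baseline is detail that an article may leave out.

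**Conclusion.** The point holds in two limited parts. The article contradicts itself on whether the economic evaluation depends on a positive trial. If the condition governs, the economic result would be absent with probability about 0.08 at a true hazard ratio of 1.60 (1 − 0.92) and about 0.54 at 1.30 (1 − 0.46). The reported QALY difference would be shifted up by 0.05–0.10 and 0.26–0.52 standard errors respectively. These shifts rest on an assumed correlation of 0.3–0.6 and on reading confirmation as a significant primary test in favour of CaPE.

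Separately, the stated interval around the ratio can be unbounded or ambiguous in sign. How likely that is depends heavily on the QALY gain. The share of negative replicates is about 6–18% for a gain of 0.03, 0.5–6% for 0.05 and under 1% for 0.08. The gains and SDs are assumptions, and the documents give none. They do not support a flat statement that the ratio interval will be uninterpretable.

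Neither part touches the primary analysis, the sample size or data collection. The sentence on comparing QALY gains at baseline is a wording error only.

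**What to change.** - In Study objectives, delete the parenthesis on the third objective so that it agrees with the Aims, the introduction and the Cost–utility analysis section.
- In Cost–utility analysis, replace the confidence interval around the ratio with incremental net monetary benefit and its 95% confidence interval over a range of thresholds. Add the cost-effectiveness plane and an acceptability curve from the bootstrap already planned. These stay defined when the QALY difference is near or below zero.
- In the same section, reword the QALY sentence to say that EQ-5D utility is compared at baseline and QALYs over the 12 months.

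The cost is three wording changes and a little extra analysis on data that will be collected anyway.

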#### Randomisation and masking

Participants will be randomised using a block randomisation technique in a 1:1 allocation to CaPE or TAU. Randomisation will be computer generated and use a random permuted block method with variable block sizes. The sample will be stratified by site, bipolar type (I or II) and self-reported biological sex, given the potential differences in recurrence rates in these groups. In line with best practice in RCTs, we have not included further stratification variables.^38^ We will assess other potential prognostic characteristics (age, duration of illness, number of previous episodes, gender) in our *a priori* subgroup analyses.

This will be an assessor-masked RCT. Owing to the nature of the interventions, clinicians in participating centres and the participants themselves cannot be masked to treatment allocation. Before assessments, participants will be asked not to reveal any information about treatment to assessors. To avoid unmasking, outcome assessors will be located separately from treatment providers, and we will assign new outcome assessors in cases of unintentional unmasking. Statistical analysis will be partially masked (knowing treatment groups, but not what each group is). The intention-to-treat analysis plan will help reduce the effect of attrition bias. Finally, registration on Clinicaltrials.gov and publication of results regardless of the outcome will both minimise reporting bias.

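### Objective 3 makes the cost-effectiveness analysis conditional on the trial confirming effectiveness, the Method section does not, and nothing reconciles the two

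*Protocol article*

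**What the plan says.** Study objectives, third objective: cost-effectiveness in a low-resource setting is to be estimated "if the RCT confirms the effectiveness of CaPE in bipolar disorder".

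Three other places carry no such condition:

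- Method, Cost–utility analysis: "A cost–utility analysis from healthcare system and societal perspectives will be conducted to establish the cost-effectiveness of CaPE compared with TAU". The service-use inventory is "completed by both treatment groups at 3, 6 and 12 months", and EQ-5D is scheduled at the same visits and at baseline.
- Abstract, Aims: a "larger multicentre RCT to confirm the clinical and cost-effectiveness of CaPE in Pakistan".
- Introduction, Psychoeducation for bipolar disorder: "we propose a confirmatory RCT to determine the clinical and cost-effectiveness of CaPE for adults with bipolar disorder".

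The article does not say which statement prevails, or what result would count as confirming effectiveness.

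**The concern.** After a null or borderline primary result, one analyst could omit the economic analysis by citing the objective, and another could run it by citing the Method section. The text leaves that choice open until the primary result is known, when it should already be fixed.

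The condition also does not match the quantity it controls. The primary outcome is time to recurrence. The planned incremental cost-effectiveness ratio is the cost difference divided by the QALY difference. CaPE could change EQ-5D scores, service use or time off work without a significant hazard ratio, or delay recurrence with little QALY gain. A decision-maker needs the cost and QALY estimates with their uncertainty in either case.

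If the condition is applied, economic estimates are seen only in trials selected for a favourable primary estimate. To the extent that the two estimates move together, those that are reported lean towards CaPE.

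**Working it through.** **Inputs.** From Sample size: 240 analysed participants (120 per arm), TAU mean time to recurrence 21.4 weeks, design hazard ratio (HR) 1.60 (written so that values above 1 favour CaPE), CaPE mean about 34.2 weeks, stated power 0.91, and minimum detectable HR 1.49 at 0.80 power. From Statistical analysis: two-sided 0.05 and 12 months of observation, taken as 52 weeks.

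**Assumptions not in the article.** Recurrence times are exponential. Confirmation means two-sided p<0.05 in favour of CaPE on the primary test. The correlation ρ between the estimated log HR and the estimated QALY difference is 0.3 to 0.7.

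**Step 1: reproduce the plan's power.** The event probability by 52 weeks is 1 − exp(−52/mean).

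- TAU: 1 − exp(−52/21.4) = 0.912
- CaPE at HR 1.60: 1 − exp(−52/34.2) = 0.781
- Events: 120 × 0.912 + 120 × 0.781 ≈ 203
- SE of the log HR: 2/√203 = 0.140
- ln(1.60)/0.140 = 0.470/0.140 ≈ 3.35
- Power: Φ(3.35 − 1.96) = 0.918, against the stated 0.91

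The same model gives a minimum detectable HR of 1.48 at 0.80 power, against the stated 1.49. It is close enough to the plan's own calculation to use.

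**Step 2: chance that the condition is met.** For a true HR, set a = 1.96 − ln(HR)/SE, with SE = 2/√events and the CaPE mean equal to 21.4 × HR. The chance is 1 − Φ(a).

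**Step 3: selection effect.** Given that the condition is met, the log HR estimate is too high on average by λ × SE, where λ = φ(a)/(1 − Φ(a)). A QALY-difference estimate correlated at ρ with the log HR estimate is then too high by ρ × λ of its own standard errors.

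| True HR | Events | P(condition met) | Analysis dropped | λ | Mean HR if met | QALY overstatement, ρ = 0.3 to 0.7 |
|---|---|---|---|---|---|---|
| 1.6 | 203 | 0.92 | 8% | 0.166 | 1.64 | 0.05–0.12 SE |
| 1.4 | 208 | 0.68 | 32% | 0.526 | 1.51 | 0.16–0.37 SE |
| 1.3 | 211 | 0.48 | 52% | 0.833 | 1.46 | 0.25–0.58 SE |
| 1.2 | 214 | 0.27 | 73% | 1.236 | 1.42 | 0.37–0.87 SE |

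Worked row, HR 1.3: SE = 2/√211 = 0.138; a = 1.96 − 0.262/0.138 ≈ 0.055; 1 − Φ(a) = 0.478; λ = 0.398/0.478 = 0.833; 0.3 × 0.833 = 0.25 and 0.7 × 0.833 = 0.58.

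**If the Method section governs,** the analysis is run with probability 1 and the last column is zero throughout.

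**The case against.** The best defence is that the objective says when the analysis is done and the Method section says how, so that only a cross-reference is missing, and that there is little sense in costing a treatment not shown to work. A condition disclosed in advance is also not the usual kind of selective reporting, where the choice follows sight of the results. Part of this stands: the mismatch may be loose drafting, and the abstract's one-line aim would naturally lose a qualifier. But someone who reads only the Method section would expect an unconditional analysis. Nor does a non-significant hazard ratio show that the treatment is ineffective: the plan's own minimum detectable value at 0.80 power is 1.49, so smaller real effects can easily miss significance.

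The defence is also right about size. At the hazard ratio for which the trial is designed, the selection effect is negligible. The larger figures apply to true effects below 1.49.

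Two stronger inferences are tempting, and the article supports neither:

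- **That the condition breaks the promise of "publication of results regardless of the outcome will both minimise reporting bias".** That sentence, under Randomisation and masking, concerns publishing results, not which analyses are run. A null primary result could be published in full with objective 3 reported as not triggered.
- **That economic data from all 300 participants would be thrown away.** Objective 2 covers quality of life without condition, so EQ-5D could still be reported. The sample size also allows for 20% attrition, so complete follow-up on all 300 is not expected.

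**Conclusion.** The inconsistency is real, and it needs no assumption: one statement of the economic aim is conditional, three are not, and the condition is undefined. That a condition based on recurrence does not match a ratio of costs to QALYs also holds, provided that confirmation refers to the primary outcome.

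A reader might infer that the plan, as it stands, biases the cost-effectiveness ratio towards CaPE. The article does not support that. The bias is one of conditional reporting, and the estimator is not biased if the analysis is always run. It arises only if the objective governs, and its size depends on reading confirmation as p<0.05 and on a correlation that the article does not give. Its direction needs that correlation to be positive, which is plausible because recurrence affects both quality of life and service use. No shift in QALYs, costs or the ratio itself can be derived from the article; the figures are in standard errors of the QALY difference only.

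The more robust consequence is the loss of the analysis: about 8% of trials at the design effect, but about half at a true hazard ratio of 1.3. The primary analysis, sample size and data collection are unaffected.

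**What to change.** Delete the parenthesis from objective 3. State in both Study objectives and Cost–utility analysis that the cost–utility analysis will be run and reported by allocated group for all randomised participants, with the planned handling of missing data, whatever the primary result. The bootstrapping, confidence intervals and sensitivity analyses already planned can carry the uncertainty without a condition.

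The economic data are collected in both arms in any case, and sample size and significance level do not change. The only cost is the analysis work after a null result.
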